**Objective:**

This study aims to determine the optimal deployment of the PPA in clinical settings (at enrollment vs delayed start) and to compare intervention outcomes with a no-intervention, observation-only condition. The PPA is designed specifically for key HIV disparity populations, including younger sexual, gender, racial, and ethnic minorities.

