**Methods:**

The Positive Peers Intervention Trial (PoPIT) is a multisite, randomized clinical trial designed to evaluate the effectiveness of the PPA as a tool for use in clinical settings. Trial arms compare the immediate deployment of the PPA with usual care and observation only. This protocol outlines a mixed methods design consisting of concurrent prospective self-report questionnaires, in-depth interviews with PPA users, and medical record review. PoPIT questionnaires include measures of social determinants of health, HIV-related stigma, perceptions of digital media use, self-efficacy, substance use, and social support. Multiple aspects of PPA intervention engagement are measured natively within the app. Outcomes include HIV National Quality Forum indicators and perceived HIV-related stigma.

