## Methods

### Study Design

Specific aims and corresponding hypotheses will be evaluated in a randomized controlled trial that compares HIV outcomes in patient groups randomized to either immediate or delayed access to the PPA. The delayed-start design is intended to ensure that both randomized study conditions receive identical study procedures, follow-up, reminders, incentives, and assessments during the first 6 months of participation. The only difference is the timing of app access. Any improvement observed in the delayed-start group during this period can therefore be attributed primarily to nonspecific effects of trial participation. The primary randomized comparison at 6 months thus estimates the incremental benefit of the app beyond these common trial effects. A greater improvement in outcomes in the immediate-start group at this point would provide evidence of a specific impact of the app.

Prospective questionnaires will be administered at baseline and at 3, 6, 9, and 12 months to provide evidence for model-specific hypotheses and the mediating effects of covariates and demographics. We have included an opportunity for patients who decline full study participation to grant permission to the PoPIT team to abstract their HIV outcomes from medical records on the same schedule as full study participants. This observation-only arm includes only the baseline questionnaire and medical record review of study outcomes. The inclusion of an observational cohort in the randomized controlled trial design strengthens external validity by enabling comparison of trial participants with the broader clinic population. By comparing outcomes from both randomized controlled trial arms with those of the observational cohort, we will gain additional insight into how trial participation may influence outcomes and how the intervention might be further adapted for a more diverse clinical population.

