### Recruitment

Eligible persons seeking care or registered with a participating clinic are invited to participate in the study through their preferred contact channel on record with the clinic. They are asked by trained clinic staff at participating sites whether they would be interested in helping to evaluate a new HIV support app in a research study. Persons who agree to participate review the informed consent document with the study staff before any study procedures. Participants can earn up to US $250 in gift cards by completing study questionnaires and interviews. Participants receive US $50 for completing the baseline questionnaire and a qualitative interview, and US $25 for completing each follow-up questionnaire. There is also a monthly raffle for ecological momentary assessment (EMA) completion, in which participants have a chance to win an additional US $25 for completing an EMA questionnaire during that month. If a person declines participation in the randomized trial, they are asked whether they would participate in the more passive observational monitoring arm, which includes a baseline questionnaire and prospective medical record data collection. Participants in the observational cohort are compensated with a US $50 gift card at the time of study consent and completion of the baseline questionnaire.

A reliance review institutional review board (IRB) system is in place, with agreements from all sites to accept the lead study site IRB for regulatory oversight. The general consent form is written in simple, plain language and is devoid of logos and colors. One study site is required to use its own institution’s regulatory language; however, study information is consistent across all sites. The primary investigative team is clearly identified in the consent form, along with corresponding contact information.

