### Enrollment, Randomization, and Data Collection Procedures

All participants are consented, enrolled, and randomized at the partner institution where they receive care, in partnership with the PoPIT staff, who are needed to set up the user’s PPA account. Specifically, following in-person consent at the partner site, all participants complete a preloaded baseline questionnaire on a study-dedicated tablet in the presence of study staff. While they are completing the questionnaire, the trial participant is randomly assigned in REDCap to either the intervention (immediate PPA start) or control (6-month delayed PPA start) arm at a 1:1 ratio. Participants randomized to the delayed-start arm receive usual clinic care before beginning the clinical intervention. Given our pilot findings indicating a stronger PPA effect on HIV viral suppression among participants in the youngest age group (ie, <24 years), we employ a block randomization strategy in which study arm assignment occurs separately for participants within the age groups 13-24 and 25-34 years.

Following randomization, site study staff assist participants randomized to the immediate-start arm in downloading the PPA from the public app store using the participant’s personal phone. Site study staff guide participants through in-app tutorials demonstrating how to use app features. Participants randomized to the delayed-start arm are provided with a folder containing general HIV self-management information and contact numbers for the clinic and the site coordinator. Data are collected via online forms (enrollment and medical record review), questionnaires, and SMS text messaging. Participants are consented and enrolled by study staff in person, and the baseline questionnaire is completed independently at the same visit. Remaining follow-up questionnaires at 3, 6, 9, and 12 months are prompted by an SMS text message or email and completed online. Participants and study staff are aware of study arm assignment. Delayed-start participants are given app access after completing the 6-month questionnaire. Site study staff follow the same procedure to assist with downloading the app and reviewing tutorials for participants in both the immediate- and delayed-start arms.

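### The observation-only cohort consists of trial decliners, so comparing it with the randomised arms cannot separate app, participation and self-selection, and the one app-free contrast is not named

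*Protocol article*

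**What the plan says.** The protocol article gives the observation-only cohort three jobs.

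- **Comparator for the intervention.** The Objective in the Abstract includes the aim "to compare intervention outcomes with a no-intervention, observation-only condition". The Methods paragraph of the Abstract puts it beside the randomised control: "Trial arms compare the immediate deployment of the PPA with usual care and observation only".
- **Evidence on trial participation.** Study Design gives the method as "By comparing outcomes from both randomized controlled trial arms with those of the observational cohort". The expected gain is worded cautiously: "we will gain additional insight into how trial participation may influence outcomes".
- **External validity.** The same section says that including the cohort "strengthens external validity by enabling comparison of trial participants with the broader clinic population".

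Two sections state who is in the cohort. Study Design: "We have included an opportunity for patients who decline full study participation to grant permission to the PoPIT team to abstract their HIV outcomes". Recruitment: "If a person declines participation in the randomized trial, they are asked whether they would participate in the more passive observational monitoring arm". Members complete the baseline questionnaire and are followed through their records on the same schedule as trial participants.

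On app exposure, the immediate arm downloads the app at enrolment. For the other arm, the section on enrolment and randomisation says: "Delayed-start participants are given app access after completing the 6-month questionnaire". Clinical outcomes are taken at 6-month intervals for 18 months (Clinical Outcomes).

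**The concern.** Randomisation protects only the immediate-versus-delayed contrast. The cohort is formed by the patient's own decision not to be randomised, so its members may differ from trial participants in ways that also bear on retention and viral suppression. A difference between a randomised arm and the cohort would then be read as an app effect (following the Abstract) or as a participation effect (following Study Design) when it is neither alone.

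The participation question has a second difficulty. The text points to both randomised arms, but one has the app from the start and the other has it after month 6. A contrast that includes app-exposed time cannot isolate participation, even if there were no self-selection.

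The description of the cohort also goes further than its membership allows. It contains only people who met the trial's eligibility criteria, declined randomisation and then consented to be observed. That is narrower than the clinic population at large.

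At stake is a non-randomised contrast being reported beside the randomised one with the same standing, in answer to an objective stated in the Abstract.

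**Working it through.** **1. Inputs from the protocol (Power Analysis).** Proportion suppressed 0.80 with the app and 0.60 in control; two-sided Z test with pooled variance; alpha .05; 106 per group; 90% power; 250 to be randomised. No size is given for the observation-only cohort.

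**2. The plan's own figure.** With unpooled variance, n = (1.960 + 1.282)² × (0.80×0.20 + 0.60×0.40) / 0.20² = 105.07, rounded up to 106 per group. With pooled variance the formula gives 109. Power at 106 per group with the pooled test is 0.894. The stated 106 is reproduced closely enough to use these inputs. It covers the two randomised groups only.

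**3. What each contrast contains.** Let A be the app effect, P the effect of trial participation, and S the selection difference (trial participants minus decliners, with neither app nor trial).

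| Contrast | Contains |
|---|---|
| Immediate − delayed, month 6 | A |
| Immediate − cohort | A + P + S |
| Delayed − cohort, months 0-6 | P + S |
| Both arms taken together (1:1) − cohort, months 0-6 | A/2 + P + S |

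Only the first row isolates a single effect, and it does not use the cohort.

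**4. App-free cells.** Two arms by three windows (0-6, 6-12 and 12-18 months) give six cells. The immediate arm has app access in all three and the delayed arm in the last two, so five of the six include the app. The only app-free cell is the delayed arm in months 0-6.

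**5. Size, with A = 0.80 − 0.60 = 0.20.** P and S are assumptions, each varied from 0 to 0.10.

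- Immediate − cohort: 0.20 + P + S, from 0.20 to 0.40.
- Delayed − cohort, months 0-6: P + S, from 0.00 to 0.20.
- Both arms together − cohort, months 0-6: 0.10 + P + S, from 0.10 to 0.30.

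With P = S = 0, the last contrast still shows 0.10, all of it due to the app.

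**6. Illustration of false signals.** Cohort size, selection gap and its direction are assumed. The test is an unadjusted two-sided pooled Z test at .05, with rejection probability Φ[(d − 1.960·SE₀)/SE₁], where d is the difference, SE₀ the pooled and SE₁ the unpooled standard error.

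*Selection only (A = P = 0):*

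- 250 vs 100, 60% vs 50%: SE₀ = 0.0586, SE₁ = 0.0588, so Φ[(0.10 − 0.1148)/0.0588] = 0.40.
- 250 vs 100, 60% vs 45%: 0.72.
- 125 vs 100: 0.32 (60% vs 50%) and 0.61 (60% vs 45%).
- 250 vs 50, 60% vs 50%: 0.26.

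*App only (P = S = 0):* both arms together, 212 at 70%, vs a cohort of 50, 100 or 125 at 60%: 0.28, 0.42 or 0.47.

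*Delayed arm vs cohort with S = 0.10 and P = 0:* 106 at 60% vs 50, 100 or 125 at 50%: 0.22, 0.30 or 0.33. The app-free contrast is therefore still open to selection.

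**The case against.** The strongest reply is that little in the protocol depends on this cohort. The specific aims do not mention it, Study Design names the randomised 6-month contrast as primary, the power analysis covers only the two randomised groups, and the planned analysis does not use it. The comparator role comes from two sentences in the Abstract. All of this stands, and it limits the point to secondary inference.

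The Study Design wording is also hedged: it offers added insight into how participation may influence outcomes, and it names a further purpose, adapting the intervention for a more diverse population. A reader might infer that the arms are to be pooled and followed against the cohort over all 18 months, so that no participation effect could be shown. The text states neither pooling nor a window. Comparing both arms could mean each arm separately, which would include the delayed arm in months 0-6, and the same section already treats that period as reflecting nonspecific trial effects. What remains is that the text does not single out that contrast for comparison with the cohort.

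The recruitment route is disclosed, and adjustment for selection may be set out in a full protocol or analysis plan that is not shown. Its absence is not counted here. Adjustment would not, however, make an app-exposed arm informative about participation alone, nor turn consenting decliners into the clinic at large.

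Finally, a reader might infer that decliners are less engaged in care and that a spurious benefit is therefore likely. The documents do not say so. Every eligible patient, decliner or not, must be newly diagnosed, out of care or unsuppressed, so even the direction of any selection gap is unknown.

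**Conclusion.** The point holds as a matter of secondary inference. The Abstract treats a self-selected group as a comparator for the intervention, and Study Design uses both randomised arms against it for the participation question and describes it more broadly than its membership supports. Immediate arm minus cohort is A + P + S. The only app-free contrast is delayed arm minus cohort in months 0-6, which is P + S, and the text neither names it nor cautions about selection.

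The size rests on assumptions. The 0.10 from the app alone uses the protocol's 0.80 and 0.60 and takes the two arms together at 6 months. The rejection probabilities, such as about 0.40 for 60% vs 50% with 250 vs 100, use an assumed cohort size and selection gap; they are illustrations, not figures from the document.

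The randomised 6-month estimate, its sample size and its test are not affected.

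**What to change.** - **Abstract (Objective and Methods) and Study Design:** call the cohort a non-randomised reference group, and keep the app-effect objective to immediate versus delayed start at 6 months.
- **Participation question:** name delayed-start arm versus cohort in months 0-6 as the contrast. Adjust or weight for data already collected in both groups: baseline questionnaire, age group, site, eligibility route (newly diagnosed, out of care or unsuppressed), and prior-year visits and viral load. Report the result as associational.
- **External-validity sentence:** describe the cohort as eligible patients who declined randomisation and consented to record review. Its outcome data can still be reported descriptively.

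The cost is rewording in three places and one adjusted analysis, with no new data collection and no change to randomisation. The downside is a weaker claim from the cohort.

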### Sample Population

The study is designed to evaluate the effects of the PPA intervention among the age group most likely to be newly diagnosed with HIV in the United States: adolescents and young adults. This cohort is challenged by a propensity for greater risk behavior, lower health literacy and management skills, and typically less favorable social determinants of health. Potential participants are identified as patients at 1 of 5 HIV care organizations serving as study sites, located across 6 priority jurisdictions where HIV transmission occurs most frequently. Patients are screened to determine whether they meet all necessary inclusion criteria for study participation (Textbox 1).

Positive Peers Intervention Trial eligibility criteria.Inclusion criteriaHIV-positive status, either newly diagnosed within the last 12 months, out of care (without an office visit in the last 12 months), or not virally suppressed (viral load >200 copies/mL within the last 12 months).Adolescents and young adults aged 13-34 receiving care at one of the study sites.Identification with a sexual, gender, racial, or ethnic minority.Participant’s capacity to provide informed consent (aged >16 years) or assent to participate (aged <16 years).Ownership of a smartphone/tablet (either iOS or Android) capable of supporting the Positive Peers mobile app.Ability to read English.Exclusion criteriaPrevious use of the Positive Peers mobile app.Adults older than age 34 at the time of enrollment.Not a patient at one of the participating clinical sites.

### Study Setting

Ending the Epidemic aims to decrease new infections by identifying PWH, increasing access to biomedical and HIV prevention interventions, and improving engagement in care for those already diagnosed [72]. The PoPIT study is being implemented at 6 study sites within high-priority jurisdictions in the United States. Three of these sites are within infectious disease clinics at academic medical centers in Texas, New Jersey, and Washington, while the remaining 3 are located at federally qualified health centers in California and Ohio.

### Recruitment

Eligible persons seeking care or registered with a participating clinic are invited to participate in the study through their preferred contact channel on record with the clinic. They are asked by trained clinic staff at participating sites whether they would be interested in helping to evaluate a new HIV support app in a research study. Persons who agree to participate review the informed consent document with the study staff before any study procedures. Participants can earn up to US $250 in gift cards by completing study questionnaires and interviews. Participants receive US $50 for completing the baseline questionnaire and a qualitative interview, and US $25 for completing each follow-up questionnaire. There is also a monthly raffle for ecological momentary assessment (EMA) completion, in which participants have a chance to win an additional US $25 for completing an EMA questionnaire during that month. If a person declines participation in the randomized trial, they are asked whether they would participate in the more passive observational monitoring arm, which includes a baseline questionnaire and prospective medical record data collection. Participants in the observational cohort are compensated with a US $50 gift card at the time of study consent and completion of the baseline questionnaire.

A reliance review institutional review board (IRB) system is in place, with agreements from all sites to accept the lead study site IRB for regulatory oversight. The general consent form is written in simple, plain language and is devoid of logos and colors. One study site is required to use its own institution’s regulatory language; however, study information is consistent across all sites. The primary investigative team is clearly identified in the consent form, along with corresponding contact information.

### Enrollment, Randomization, and Data Collection Procedures

All participants are consented, enrolled, and randomized at the partner institution where they receive care, in partnership with the PoPIT staff, who are needed to set up the user’s PPA account. Specifically, following in-person consent at the partner site, all participants complete a preloaded baseline questionnaire on a study-dedicated tablet in the presence of study staff. While they are completing the questionnaire, the trial participant is randomly assigned in REDCap to either the intervention (immediate PPA start) or control (6-month delayed PPA start) arm at a 1:1 ratio. Participants randomized to the delayed-start arm receive usual clinic care before beginning the clinical intervention. Given our pilot findings indicating a stronger PPA effect on HIV viral suppression among participants in the youngest age group (ie, <24 years), we employ a block randomization strategy in which study arm assignment occurs separately for participants within the age groups 13-24 and 25-34 years.

Following randomization, site study staff assist participants randomized to the immediate-start arm in downloading the PPA from the public app store using the participant’s personal phone. Site study staff guide participants through in-app tutorials demonstrating how to use app features. Participants randomized to the delayed-start arm are provided with a folder containing general HIV self-management information and contact numbers for the clinic and the site coordinator. Data are collected via online forms (enrollment and medical record review), questionnaires, and SMS text messaging. Participants are consented and enrolled by study staff in person, and the baseline questionnaire is completed independently at the same visit. Remaining follow-up questionnaires at 3, 6, 9, and 12 months are prompted by an SMS text message or email and completed online. Participants and study staff are aware of study arm assignment. Delayed-start participants are given app access after completing the 6-month questionnaire. Site study staff follow the same procedure to assist with downloading the app and reviewing tutorials for participants in both the immediate- and delayed-start arms.

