### Quantitative Data Collection and Measures

Data collection is planned for a total of 18 months for each participant. Three modes of data collection are used in the study. First, site staff collect medical record data, including date of diagnosis, HIV viral load, T-cell counts, and office visit dates, for the 12 months before enrollment and for 18 months after enrollment.

Second, participants receive an email or SMS text message notification to complete follow-up electronic questionnaires at 3, 6, 9, and 12 months after enrollment. Automated reminders are sent on the scheduled completion date; if the questionnaire is not completed, additional reminders are sent 1 week and 2 weeks later. If the questionnaire coincides with an office visit or cannot be completed remotely for any other reason, study staff can administer the pending questionnaire on site using a laptop or iPad (Apple Inc). Delayed-start participants are onboarded to the app, either in person or remotely by site staff, 6 months after enrollment. This group completes baseline, 3-month, and 6-month questionnaires before downloading and initiating app use.

Third, during the intervention period, EMAs are used to collect in-the-moment information about app use (eg, “Is the Positive Peers mobile app currently downloaded to your phone?”) and related perceptions. PPA provides a natural technological interface through which such perceptions or behaviors, and their correlates within the app or the broader social environment, can be assessed in a nuanced, dynamic, and longitudinal framework.

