#### Clinical Outcomes

Retention in HIV care and viral suppression are measured using standardized performance measures developed by the HRSA/HIV/AIDS Bureau [89]. Measures selected for this study are retention in HIV medical care (2 or more visits separated by at least 90 days for HIV care within the measurement year) and HIV load suppression (the most recent viral load <200 copies/mL during the measurement year). Values for outcome variables (engagement in care and viral suppression) are derived from a retrospective medical record review conducted by site study staff using a study-specific form. Engagement in care is determined by at least one office visit with an HIV clinician per 6-month interval for 12 months before and 6 months after study enrollment. Viral suppression is determined by assessing the participant’s viral load, as noted in laboratory values, typically required at least every 6 months per the standard of care. A value of <200 copies/mL is considered suppressed. Values for each variable are established for the year before study enrollment, at baseline enrollment, and then at 6-month intervals for 18 months.

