### Planned Statistical Analysis

Aims 1 and 2 entail data collection and analysis to provide evidence of PPA effectiveness. Outcomes include retention in HIV care (proportion of enrolled patients with laboratory results in each 6-month period of the study), HIV load suppression (proportion of enrolled patients whose viral load measurement at 6 months in the study is <200 copies/mL), as well as self-reported psychosocial variables, specifically perceived technology affordances, attitudes toward technology, and self-efficacy for managing chronic conditions. We expect that key demographics, technology covariates, and PPA use will predict self-efficacy, which will be directly associated with (1) retention in care, (2) viral suppression, and (3) HIV-related perceived stigma. Additionally, we plan to test potential covariate mediation and examine theoretical linkages in our model of PPA effects.

Analyses of repeated measures will be performed using generalized linear mixed-effects models with a logit link function for binary outcomes (ie, viral suppression and engagement in care) and linear mixed-effects models for continuous outcomes (eg, perceived stigma, resilience). Time will be treated as a fixed, repeated factor within patients, and patient-specific random effects will be included to account for within-patient correlation. To appropriately model the hierarchical structure of observations nested within patients and patients nested within sites, the site will be included as a random effect, providing an estimate of between-site variability. Multilevel mediation models will be used to evaluate potential mediating effects of covariates. *P* values will be adjusted using Bonferroni or Benjamini-Hochberg correction procedures to control the family-wise type I error rate due to multiple comparisons across distinct psychological outcomes.

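### Age stratum and eligibility route are absent from the stated 6-month model terms; prespecifying both would bring a modest gain in precision and credibility, and there is no validity problem

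*Protocol article*

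**What the plan says.** **Who enters.** Under Sample Population (Textbox 1), a participant qualifies by being "either newly diagnosed within the last 12 months, out of care (without an office visit in the last 12 months), or not virally suppressed". The three routes are joined by "or" and can overlap.

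**How they are allocated.** Under Enrollment, Randomization, and Data Collection Procedures, allocation is 1:1 and blocked, and "study arm assignment occurs separately for participants within the age groups 13-24 and 25-34 years". The reason given is a stronger pilot effect in the youngest group. No other stratification factor is named.

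**What is compared.** Under Study Design: "The primary randomized comparison at 6 months thus estimates the incremental benefit of the app beyond these common trial effects".

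**How it is modelled.** Under Planned Statistical Analysis: "Time will be treated as a fixed, repeated factor within patients, and patient-specific random effects will be included to account for within-patient correlation". In addition, "the site will be included as a random effect, providing an estimate of between-site variability". Covariates appear there only as predictors or mediators, for example "We expect that key demographics, technology covariates, and PPA use will predict self-efficacy". None is named as an adjustment of the comparison between arms.

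**What is already collected.** Under Quantitative Data Collection and Measures, site staff abstract records "including date of diagnosis, HIV viral load, T-cell counts, and office visit dates, for the 12 months before enrollment". Under Clinical Outcomes: "Values for each variable are established for the year before study enrollment, at baseline enrollment, and then at 6-month intervals for 18 months".

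**The concern.** The three routes probably carry different outlooks at 6 months. A new diagnosis leads into first treatment, whereas the other two routes are defined by a lapse in care or by a viral load above the threshold. The plan's own scoring strengthens the link: under Power Analysis, a patient with no documented visit in the assessment period counts as out of care and as unsuppressed. A history of missed visits, which defines the second route, therefore bears on both clinical outcomes.

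If route is prognostic and neither balanced nor adjusted for, the 6-month contrast carries variation that could be removed with data the trial already has. The age stratum is a simpler matter: it was used to allocate, so the analysis would ordinarily carry it.

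Credibility is also at stake. Participants and staff know the assignment. If a noticeable route imbalance appears and adjustment is chosen only then, the choice can look driven by the data.

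**Working it through.** **1. The plan's own figure.** Inputs from Power Analysis: 60% vs 80%, two-sided alpha 0.05, 90% power, 106 per arm.
- Unpooled normal formula: (1.960 + 1.282)² × (0.24 + 0.16) / 0.20² = 105.07, so 106 per arm.
- The pooled formula gives 109 per arm, and the pooled Z test at 106 per arm has power 0.894.
- The stated 106 is therefore reproduced within rounding of method.

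**2. Assumptions.** The article gives neither route shares nor suppression by route. I assume one third per route and control suppression averaging the plan's 60%: from 75/52.5/52.5% (gap 22.5 points) to 85/47.5/47.5% (gap 37.5 points), in the order newly diagnosed / out of care / viremic. A common odds ratio is set so that the treated average is 80%:
- low end: odds ratio 2.77, treated rates 89.3/75.4/75.4%;
- high end: odds ratio 2.96, treated rates 94.4/72.8/72.8%.

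**3. How far route shares can drift.** The standard deviation of the between-arm difference in a one-third share is √(2 × 1/3 × 2/3 / n). This is 6.5 points at 106 per arm and 6.0 points at 125. A difference of 10 points or more has probability about 12% and 9% respectively.

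**4. What that does to the suppression difference, at 125 per arm (half of the planned 250).** With one distinct route of share 1/3, the between-route variance within an arm is gap² × 2/9.

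| | Control arm | Treated arm | Sum | 1.96 × √(sum/125) |
|---|---|---|---|---|
| Low end | 0.0113 | 0.0043 | 0.0155 | ±2.2 points |
| High end | 0.0313 | 0.0103 | 0.0416 | ±3.6 points |

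**5. Set against the whole standard error.** The unadjusted variance is (0.24 + 0.16)/125 = 0.0032, so the 95% half-width is 1.96 × √0.0032 = 11.1 points. The route component is a share of that variance: 0.0155/0.40 = 3.9% and 0.0416/0.40 = 10.4%. Removing all of it would bring the half-width to about 10.9 and 10.5 points. This is an upper bound on the gain.

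**6. Power and type I error, by simulation.** The comparison is an unadjusted pooled Z test against a Cochran-Mantel-Haenszel test stratified by route, at 106 per arm.
- Low end of the assumed range: 0.896 to 0.904. High end: 0.896 to 0.920 (40,000 runs each).
- Four further scenarios with the same 60% control average, including unequal shares of 40/20/40%: 0.895–0.898 to 0.905–0.921 (20,000 runs each).
- In those four scenarios type I error is 0.048–0.052 with or without adjustment.

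The comparator is an unadjusted test, not the planned mixed model, so these gains are upper guides. No corresponding calculation was made for retention.

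**The case against.** **The article is condensed and the analysis plan is not shown.** A covariate list is normally in the analysis plan. The modelling paragraph does not spell out a treatment-arm term either, so its silence cannot be read as exclusion. This stands: a reader might infer that the trial has decided to ignore route, and the document does not show that. What remains is narrower. The article does name specific model terms, and the age stratum and route are not among them.

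**Chance imbalance is ordinary sampling error.** This also stands. A reader might infer that the 6-month result would be biased or its test invalid. Randomisation rules that out: the imbalance is random, the standard error covers it, and simulated type I error stays near 0.05.

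**The shift can be made to look larger than it is.** One could multiply a 95% share imbalance of 11.7 points (1.96 × √(2 × 1/3 × 2/3 / 125)) by a 40-point gap and obtain ±4.7 points. That applies 40 points to both arms, whereas the widest control gap assumed here is 37.5 points and a common odds ratio shrinks the treated gap to about 22. The upper figure is then ±3.6. Setting it against the planned 20 points alone also hides that it already lies inside the ±11-point interval.

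**Baseline data and site may do some of the work.** Suppression and engagement are recorded before and at enrolment. If baseline is one of the model's time points, an arm-by-time contrast could absorb part of the imbalance. That is fair and lowers the expected gain by an amount not computed here. It may not absorb all of it, because a newly diagnosed and a long-term viremic patient can both be unsuppressed at entry with different outlooks.

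**Conclusion.** The point holds as a modest, nearly free improvement. Allocation is stratified by age only, and the stated terms (time, patient, site) include neither the age stratum nor the eligibility route.

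The validity of the 6-month comparison is not in question. The cost of leaving route out is at most about 4–10% of the variance of the suppression difference and about 1–3 points of power at 106 per arm against an unadjusted test, and less if baseline suppression or site already carries part of the same information. The second cost is credibility, should an imbalance be adjusted for only after it is seen.

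The size depends wholly on the assumed shares, the assumed 22.5- to 37.5-point control gap and the common odds ratio, none of which the article supplies. Smaller differences between routes would shrink the gain towards nothing. That route also matters for retention is plausible but was not quantified.

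**What to change.** Check whether the full analysis plan already lists these covariates. If it does not, add the following before any outcome is examined by arm:

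- Derive a three-level eligibility route (newly diagnosed / out of care / viremic) from screening data and the prior-12-month records, with a fixed order for people who meet more than one criterion.
- Enter the age stratum and the route as fixed covariates in the 6-month models for viral suppression and retention.
- Use baseline suppression where available, either as the baseline response in the repeated-measures model or as a covariate, but not both. State how a missing value is handled so that nobody drops out of the analysis.
- Report the marginal 6-month difference in proportions from the adjusted model, so that the result is on the scale used for the sample size.

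Randomisation does not change. The cost is one derived variable, one degree of freedom for age, two for route and one or two for baseline suppression, plus analysis-plan wording. No additional patients and no new data collection are needed.
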